#### Physical activity level and sleep parameters

Physical activity level and sleep parameters will be assessed by a tri-axial accelerometer (GT9X Actigraph, Pensacola, USA). For the physical activity assessment, patients will wear the accelerometer [83] for at least 7 days, with a sampling rate of 100 Hz. The patient will be instructed to not change their routine and to wear it from the moment of waking to sleeping time, removing it just to shower. The equipment will be worn on the waist (right side) as directed by the manufacturer. The observed parameters for physical activity will be sedentary time, active time, time spent on different physical activity intensities, energy expenditure, and number of steps. For the sleep parameters, patients will be instructed to not change their routine and to remove the accelerometer just to shower (sleep with accelerometer). The equipment will be worn on the wrist (non-dominant side) as directed by the manufacturer. The observed parameters for sleep will be (1) total sleep time (i.e., total sleep time, not including awaking time in bed), calculated as the total number of sleeping minutes from ‘lights off’ to ‘lights on’; (2) sleep onset latency (i.e., amount of time spent in the transition from wakefulness to sleep in minutes), a higher sleep onset latency indicates disturbed sleep (difficulty falling asleep); (3) sleep efficiency (i.e., ratio of total sleep time to bed time expressed as a percentage), a lower sleep efficiency indicates a lower sleep quality; (4) wake after sleep onset (i.e., sum of all moments (minutes) between onset of sleep and end of sleep – early onset); wakefulness after sleep onset will be recorded in minutes, a longer awake period after sleep onset indicates a more fragmented sleep; and (5) total activity count (i.e., sum of activity counts every night during sleep, on average, during the 7 days of use of ActiGraph) [84]. Regarding the use of the accelerometer to assess habitual physical activity and sleep, patients will receive a copy of the user guide, highlighting the importance of wearing it for 7 days, as well as the correct moment and position of use.

#### Clinical outcomes – Body composition

Body weight will be assessed using an electronic scale (W200, Welmy, Brazil). Height will be measured using a fixed stadiometer (Sanny, São Paulo, Brazil) with an accuracy of 0.1 cm. Weight and height values will be used to calculate the BMI. Measurements of hip and waist circumference will be obtained with the use of an anthropometric metal tape with precision of 0.1 cm. All anthropometric measures will be performed following the standardization described by Guerra et al. [49].

#### Treatment costs

Treatment cost for each patient will be determined using the methods described by Codogno [50, 54]. At the end of the trial, the demands for services and medicines recorded on medical records throughout the 6 months of the intervention period will be considered. The following information will be obtained: medicines supplied to the patient, laboratory tests performed, and the number of consultations throughout the intervention period. In addition, patient costs will encompass the cost of administrative and maintenance services related to the BHU where the procedures will be performed. The costs stipulated for these services and the number of patients attended will be added to the costs of each patient, according to the number of days that they visited the BHU over the 6-month period. In order to transform the procedures into actual currency, the values informed by the Municipal Health Department for the year 2018 will be used.

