**Discussion:**

This study was selected in the call of public policy programs for the Brazilian Unified National Health System – “PPSUS 2015”. To our knowledge, this is the first pragmatic trial to test the effect of adding AEMC to the pharmacological treatment of patients with depression and to evaluate the possible reductions in depression symptoms and healthcare costs.

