### Setting

Patients with depression will be recruited in the southern region of the São Paulo city at the Basic Health Unit (BHU; i.e., Arariba Park) in the state of São Paulo, Brazil. This BHU is part of the Brazilian Unified National Health System. First, patients will be referred by the physician team of the BHU if they fulfil the criteria of being 40 years and older, being treated for depression, and have no absolute contraindication to perform physical exercise. After the initial screening, patients will be fully informed of the procedures involved in the present trial and invited to sign an informed consent form. Participants will visit the laboratory on six occasions to perform the following assessments (Fig. 2):Visit 1: Consent form and anamnesis, Mini International Neuropsychiatric Interview (MINI) [52], and MADRS scale [28]. The number of depressive episodes in life and medicine dosage in the last 3 months (necessary clinical adjustments) [53] will be assessed by a trained psychiatrist researcher. Patients diagnosed with depression (single episode or recurrent episodes) will be referred to Visit 2. Patients will be informed that they may terminate their participation in this trial at any time, regardless of the reason.Visit 2: Questionnaire of cognitive function, suicidal ideation and behavior, hopelessness, and sleep quality.Visit 3: Blood samples after a 12 h fasting, functional tests, and instructions to use the accelerometer (GT9X ActiGraph accelerometer, Pensacola, USA) to assess sleep quality.Visit 4: these visits will be used to estimate the typical error of the functional tests (TUG test, TUG cognitive test, handgrip strength, 6-min walk test, body weight, hip and waist circumference); an interval of 48 h will be granted between Visits 3 and 4.Visit 5: Ergometric test and presence of absolute contraindications to exercise.Visit 6: MRI of the brain and instructions to use the accelerometer (GT9X ActiGraph accelerometer, Pensacola, USA) to assess physical activity level.

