**Fig. 2 Fig2:**
[figure not shown]
Study design. First 4 weeks, the recruitment and initial test. For 24 weeks, the intervention period – training. Final 2 weeks, the Final tests. Visit 1 (V1): Consent form, Mini International Neuropsychiatric Interview (MINI), MADRS, number of depressive episodes in life, medicine dosage in the last 3 months (necessary clinical adjustments), and anamnesis. Visit 2 (V2): Questionnaire of cognition function, suicidal ideation behavior and sleep; Visit 3 (V3): Blood sample, functional tests, and accelerometer (sleep); Visit 4 (V4): functional tests. Visit 5 (V5): cardiorespiratory parameters; Visit 6 (V6): MRI of the brain and sleep quality (physical activity). After 24 weeks of intervention, all of the experimental groups will be reassessed at visit 7 to visit 11 (V7 to V11). V7: MRI of the brain and accelerometer (sleep); V8: blood sample; V9: MADRS, number of depressive episodes and medicine dosage; V10: Questionnaire of Cognition function, suicidal ideation behavior, sleep; V11: Functional tests and accelerometer (physical activity). At the end of the study, patient treatment costs will be estimated consulting the medical records of each patient. *HC* hip circumference, *WC* waist circumference

After 24 weeks of intervention, experimental groups will be reassessed in five visits (Visits 7–11; Fig. 2):Visit 7: MRI and accelerometer to assess sleep quality.Visit 8: Blood samples after 12 h of fasting.Visit 9: MADRS and necessary adjustments on medicine dosage [53] will be verified.Visit 10: Questionnaire of cognitive function, suicidal ideation and behavior, hopelessness, and sleep quality.Visit 11: Functional tests and accelerometer to assess the physical activity level.

At the end of the study, the patient treatment costs will be estimated [50, 54] by consulting the medical records of each patient.

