### Data analysis and power calculations

The Shapiro–Wilk and Levene’s tests will be used to determine normality and variance equality, respectively. Non-normal data will be log transformed. If the transformation does not produce a normal distribution, the effect of influential points in data analyses will be tested. If influential points change the interpretation of the results, they will be manually removed. Linear mixed models having group and time as fixed factors and patients as a random factor will be performed for each outcome (MADRS, clinical outcomes, hippocampal volume, brain-derived neurotrophic factor, cardiopulmonary parameters, lipid profile, and treatment costs) and domain (especially in clinical outcomes) [85]. In case an outcome presents pre-experimental period differences between groups, determined by a regular one-way ANOVA, an ANCOVA will be implemented having pre-experimental period values as covariates, group as a fixed factor, and patients as a random factor. An intention-to-treat analysis will also be performed in case of a high incidence of missing values, using linear mixed models; the first analysis will be performed removing the missing values, while the second analysis will be performed incorporating the missing data points to determine the impact of missing values in the overall results. Whenever a significant F-value is obtained, a post hoc test with a Tukey’s adjustment will be performed. In addition, within-group (pre- to post-changes) and between-group effect sizes will be calculated using Cohen’s d [86] for each outcome. Effect sizes will be classified as small (≤ 0.49), medium (0.50–0.79), and large (≥ 0.80). Finally, the level of significance adopted in the present study for all analyses will be *P* ≤ 0.05. Data will be presented as mean ± SD. SAS 9.2^®^ software (Institute Inc., Cary, NC, USA) will be used for the statistical analyses described. Considering the importance of the control of the error rates, typical error and coefficient of variation of the assessments will be performed under test and retest conditions in a sub-sample (10 subjects).

For the primary outcome (MADRS) the verification of status of depression (depressed, partial remission, full remission) and the number of patients in remission (< 10 points MADRS) will be verified [14, 87].

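### Treatment costs are recorded once per patient, for the intervention months only, so the time model, baseline ANCOVA and pre-to-post effect size planned for them cannot be computed

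*Protocol article*

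**What the plan says.** All references are to the protocol article.

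- **What is collected.** Treatment costs takes services and medicines "recorded on medical records throughout the 6 months of the intervention period will be considered". The items are "medicines supplied to the patient, laboratory tests performed, and the number of consultations throughout the intervention period". Administrative and maintenance costs of the health unit are added "according to the number of days that they visited the BHU over the 6-month period". Everything is priced with 2018 municipal values.
- **When.** The text after the Fig. 2 legend says: "At the end of the study, the patient treatment costs will be estimated". None of the baseline Visits 1 to 6 in Setting records costs. The nearest item, at Visit 1, is "The number of depressive episodes in life and medicine dosage in the last 3 months".
- **How it is analysed.** Data analysis and power calculations says: "Linear mixed models having group and time as fixed factors and patients as a random factor will be performed for each outcome". The list of outcomes that follows ends with "cardiopulmonary parameters, lipid profile, and treatment costs". The same paragraph tests each outcome for baseline differences by one-way ANOVA, switches to an ANCOVA on pre-experimental values if they differ, and asks for within-group pre-to-post and between-group Cohen's d for each outcome.
- **What is claimed.** Study design puts treatment costs in the list of changes to be assessed. The abstract's Discussion says the trial will "evaluate the possible reductions in depression symptoms and healthcare costs".

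**The concern.** The data section and the analysis section describe different outcomes. One gives a single 6-month total per patient; the other treats cost as measured before and after the intervention. A separate analysis plan could reword the model, but it could not supply cost data that the protocol does not collect.

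If nothing changes, the cost analysis will have to be improvised after the data are in. The article intends this result to inform health policy, and cost data are often skewed, so the choice of analysis can affect the answer. Patients' earlier use of services is also likely to predict their later use, and the plan leaves that information in the charts.

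**Working it through.** The article gives no cost SD, target difference or power, so there is no planned figure to reproduce. The check sets what is collected against what is planned, then sizes the loss of precision.

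**1. Observations per patient.** Services, medicines, tests, consultations and health-unit days all refer to the 6 intervention months. That gives one cost value per patient and no pre-intervention value, for all 75 patients.

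**2. What one value per patient allows.**

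| Planned element | Needs | Computable for costs? |
|---|---|---|
| Time effect, group-by-time interaction | At least two time points | No |
| Patient random effect | Repeated values per patient | No; not separable from the residual |
| Baseline one-way ANOVA | Pre-intervention value | No |
| ANCOVA on pre-experimental value | Pre-intervention value | No |
| Within-group pre-to-post Cohen's d | Pre and post values | No |
| Between-group Cohen's d, arm comparison of 6-month cost | One value per patient | Yes |

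**3. Precision of what remains.** Inputs: 25 per arm (stated); two-sided alpha 0.05 and 80% power (chosen for illustration); normal approximation for two arms. The detectable standardised difference is d = sqrt(2/n) × (1.960 + 0.842).

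- n = 25: sqrt(0.08) × 2.802 = 0.283 × 2.802 = 0.79. Power is 0.42 at d = 0.5 and 0.81 at d = 0.8.
- n = 18 (25 × 0.7 = 17.5, from the stated drop-out of about 30%): 0.333 × 2.802 = 0.93.

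**4. Gain from adjusting for a matching prior 6-month cost.** In a linear model the standard error is multiplied by sqrt(1 − r²), where r is the correlation between prior and intervention-period cost. The article gives no r for costs, so the range is an assumption.

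| r | sqrt(1 − r²) | Fall in standard error | Detectable d, 25 per arm | Detectable d, 18 per arm |
|---|---|---|---|---|
| none (as planned) | 1 | – | 0.79 | 0.93 |
| 0.3 | 0.954 | 5% | 0.76 | 0.89 |
| 0.5 | 0.866 | 13% | 0.69 | 0.81 |
| 0.7 | 0.714 | 29% | 0.57 | 0.67 |

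The last row is 0.792 × 0.714 = 0.57 and 0.934 × 0.714 = 0.67.

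**The case against.** The strongest reply is that a randomised trial needs no baseline cost. The control group is randomised (Randomization) and keeps its regular visits to the health unit over the same months (Interventions). A lower 6-month cost in an exercise arm than in control is therefore an unbiased estimate of a reduction due to exercise. The abstract's Background and the hypothesis closing the Background section frame costs as a comparison between arms. **This stands.** A reader might infer that the aim of showing a cost reduction cannot be met; the article does not support that, because it never says the reduction is measured from a pre-trial level.

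A reader might also infer that chance differences in prior service use would bias the comparison, since allocation is stratified only on MADRS score and number of episodes. That does not follow either. Randomisation balances prior use in expectation, and chance imbalance is already reflected in the standard error. The plan also provides for log transformation and a check of influential points, so heavy users are not simply ignored.

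It can further be said that costs are one entry in a generic sentence covering all outcomes, and that they are a secondary outcome. That limits the weight of the point, but treatment costs are named explicitly, so the conflict is in the text.

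Finally, time could mean months within the intervention. Nothing says so, the costs are described as 6-month quantities, and monthly values would still give no pre-to-post contrast. The medicine dosage recorded at Visit 1 does not fill the gap: it is not a cost, covers 3 months, and leaves out tests and consultations.

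**Conclusion.** The point holds as an inconsistency between Treatment costs, Data analysis and power calculations, and Study design. For this outcome the time model, the baseline check with its ANCOVA fallback and the pre-to-post effect size cannot be run as written. This rests on the text alone and needs no numerical assumption.

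The comparison of 6-month costs between arms survives and is valid. What is lost is any statement about change from pre-trial cost, and precision: 5% to 29% of the standard error over r = 0.3 to 0.7. That range is assumed and relies on a linear model, which skewed costs may fit poorly. At r = 0.7 the gain would equal 1/(1 − 0.49) = 1.96 times the sample size, but that is the top of the assumed range (1/0.91 = 1.10 at r = 0.3) and should not be quoted as the expected gain.

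The inconsistency should be corrected before the trial starts. It concerns a secondary outcome and does not touch the primary analysis.

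**What to change.** **Preferred.** In Treatment costs, extract the same items (medicines supplied, laboratory tests, consultations, days at the health unit) from the same medical records for the 6 months before randomisation, priced with the same 2018 values. In Data analysis and power calculations, state that intervention-period cost is compared between arms adjusted for prior-period cost, regardless of whether a baseline test shows a difference. The pre-to-post effect sizes then become computable as well.

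*Cost:* one more 6-month look-back in charts that will be opened anyway, and a short edit. Trial status reports that no participants have been included. The downside is that some patients may have incomplete earlier records at this health unit.

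**Otherwise.** Remove treatment costs from the time model, the ANCOVA fallback and the pre-to-post effect sizes, and from the list of changes in Study design. State the cost analysis as a between-group comparison of 6-month costs, and make clear that any reduction is relative to the control group. This costs only a text edit, but forgoes the gain in precision.

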**Fig. 1 Fig1:**
[figure not shown]
Template of recommended content for the schedule of enrolment, interventions, and assessments

The primary outcome will be the change in the Montgomery-Åsberg Depression Scale (MADRS) score [28]. Secondary outcomes will be (1) cognitive function, assessed by Frontal Assessment Battery score [29], Trail Making Test A and B score [30], Rey’s Auditory-Verbal Learning Test (RAVLT) score [31], Digit Symbol Substitution Test score [32], Montreal Cognitive Assessment (MoCA) score [33], and Stroop test score [34]); (2) hippocampal volume assessed by magnetic resonance imaging (MRI) [35]; (3) BDNF expression [36]; (4) sleep parameters assessed by Pittsburgh Sleep Quality Index score [37], sleep quality assessment by accelerometry and the Biological Rhythms Interview of Assessment in Neuropsychiatry (BRIAN) score [38]; (5) cardiovascular risk assessed by global cardiovascular score, metabolic syndrome, waist circumference, blood pressure, lipid profile (total cholesterol, HDL cholesterol, LDL cholesterol, triglycerides), and glycemia [39, 40]; (6) suicidal ideation and behavior assessed by the Scale Columbia of Suicide score [41] and Scale of Hopelessness score [42]); (7) functionality assessed by gait linear spatial variables [43, 44], Timed Up and Go test (TUG) score [45], TUG cognitive score [46], handgrip strength [47], 6-min walk test [48] physical activity levels (sedentary time, active time, time spent in different physical activity intensities, energy expenditure, and number of steps per day), body weight, and hip and waist circumference [49]; and (8) treatment costs including laboratory procedures, medicines, and doctor consultations per patient [50].

The study will be conducted in accordance with theDeclaration of Helsinki revised in 2008 [51] and approved by the ethics committees of the Department of Health of the city of São Paulo and of the Hospital Israelita Albert Einstein, Certificate of Ethical Appreciation Presentation (PCEA) number 64888017.3.0000.0086. Trial registration is RBR-9zgxzd.

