Together with the RPE, the two-sided scales of affective valence and perception of activation will be used [60]. The affective response will be assessed using the Feeling Scale (FS). FS is a single-item scale of 11 dimensions, ranging from − 5 to + 5, commonly used to measure affective valence (pleasure/displeasure) during exercise [60]. Patients will receive standardized instructions related to the use of FS prior to the exercise session. When explaining the FS, patients should understand that, while performing exercise, it is very common to feel a change in basic affect. Some people feel the exercise as pleasurable while others feel the exercise as unpleasant. Additionally, they will be informed that it is possible for a person to experience varying pleasure and displeasure during the exercise duration [48].

In all physical exercise sessions, four exercise scientists will prescribe and monitor the interventions. Exercise scientists have already completed a 20 h workshop to standardize exercise prescription protocols.

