## Discussion

The present study has the objective to verify if patients with depression randomized into one of two physical exercise interventions (AEMC or CAE) combined with traditional drug treatment will present distinct improvements in depression symptoms (MADRS). In addition, different outcomes commonly altered by depression and with the potential to be reversed by physical exercise (e.g., cognitive function, hippocampal volume, brain-derived neurotrophic factor, sleep parameters, cardiovascular risk parameters, suicidal behavior, functionality, and treatment costs) will be evaluated.

From an operational standpoint, a pilot study involving 45 healthy elderly people was carried out in 2017, considering interventions with AEMC (two levels) and CAE (stationary cycling). Data from the pilot study are under analysis, but greater improvements with regards to cognitive and motor aspects were observed in the group undergoing exercises with greater motor complexity. In addition, training interventions produced very high exercise adherence (95%), which may be a differential, considering the difficulties in maintaining adherence during a traditional physical exercise program [89]. The main objective of this pilot study was to establish training routines and assessments and to provide logistical experiences between the parties involved (BHU, University, institutions involved in implementing training interventions and evaluations, and researchers) for the development of the proposal with patients with depression.

To our knowledge, this is the first study to test the effect of adding physical exercise to traditional treatment in patients with depression in a primary health care setting in Brazil. In addition, the use of aerobic exercises with insertion of activities with progressively higher motor complexity has not yet been tested in this population. Considering that exercises with high motor complexity may promote changes in cortical activation [90] and possibly increase the volume of associated encephalic structures (i.e., hippocampus) [27] in healthy individuals, assessing such adaptations in patients with depression is of great interest for clinical practice and public policies.

Finally, determining the impact of physical exercise programs on the treatment costs of patients with depression in Brazil may lead to new polices on how to treat them while decreasing the associated costs [2].

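### The treatment-cost outcome leaves out the cost of delivering the exercise programmes, and its planned analysis needs a pre-intervention cost that is never collected

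*Protocol article*

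**What the plan says.** The outcome list under Study design gives the eighth group of secondary outcomes as "treatment costs including laboratory procedures, medicines, and doctor consultations per patient". The Treatment costs section repeats these items ("The following information will be obtained: medicines supplied to the patient, laboratory tests performed, and the number of consultations throughout the intervention period") and fixes source and window: "the demands for services and medicines recorded on medical records throughout the 6 months of the intervention period will be considered". One further component is added: "patient costs will encompass the cost of administrative and maintenance services related to the BHU where the procedures will be performed". It is shared out "according to the number of days that they visited the BHU over the 6-month period".

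The Interventions section places both exercise programmes at a Social Service of Commerce unit, not at the BHU, in sessions of about 60 min, twice a week for 24 weeks. On staffing it says: "In all physical exercise sessions, four exercise scientists will prescribe and monitor the interventions". Control patients do no exercise training.

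Data analysis and power calculations includes costs in its list of outcomes ("cardiopulmonary parameters, lipid profile, and treatment costs") for a linear mixed model with group and time as fixed factors. An ANCOVA on pre-intervention values replaces it where groups differ at baseline. Pre-to-post effect sizes are planned for every outcome.

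The Discussion states the intended use: "determining the impact of physical exercise programs on the treatment costs of patients with depression in Brazil may lead to new polices". The abstract also speaks of possible reductions in healthcare costs, and Ethics and dissemination calls for a report aimed at managing the national health system.

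**The concern.** A health system that adopts either programme must have its sessions staffed, housed and equipped by someone. The cost measure contains none of this. Control patients have no such cost, so the omission works in one direction only: each exercise arm looks cheaper against control than it is. Since the result is meant to inform policy, a saving in BHU care could be presented as a saving in treatment cost when the programme that produced it was never counted.

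The second problem is whether the analysis can be run at all. A group-and-time model, an ANCOVA on pre values and a pre-to-post effect size all need a cost from before the intervention, and the costing section provides none.

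**Working it through.** The plan states no cost figure, so there is nothing to reproduce. The check has three parts.

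**1. Does any cost component capture the exercise programme?**

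| Component | Source | Captures exercise delivery? |
|---|---|---|
| Medicines, tests, consultations | Treatment costs; outcome list under Study design | No |
| BHU overhead, allocated by days of BHU attendance | Treatment costs | No; sessions are at another site |
| Staff, room and equipment for sessions | Not listed | – |

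Delivery cost is zero in control and positive in both exercise arms. A total that leaves it out is too low in those arms by exactly that cost.

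**2. How much resource is left out?** Inputs: 24 weeks, 2 sessions a week, about 1 h each (Interventions); 4 staff per session (Interventions); 25 patients per group (Data analysis and power calculations).

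- Sessions: 24 x 2 = 48.
- Supervision per session stream: 48 x 1 h x 4 = 192 staff-hours.
- All 50 exercise patients share the sessions: 192 / 50 = 3.84 staff-hours per patient.
- Each arm of 25 has its own sessions: 192 / 25 = 7.68 staff-hours per patient.
- Control: 0.

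Smaller classes would raise the figure, but class size is not stated. Room, equipment and heart-rate monitors come on top.

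No wage is given. Purely as an assumption, 5 to 40 currency units per staff-hour gives:

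- 50 sharing: 3.84 x 5 = 19.2 to 3.84 x 40 = 153.6 units per patient.
- 25 sharing: 7.68 x 5 = 38.4 to 7.68 x 40 = 307.2 units per patient.

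The document gives neither a usual-care cost nor an expected saving to set against these amounts.

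**3. Can the planned cost analysis be run?**

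- Collected: costs over the 6 intervention months only, one total per patient.
- Needed: a time factor, or a pre-intervention covariate, and a pre-to-post effect size.

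Visit 1 (Setting) records medicine dosage over the previous 3 months, but that is not a cost and does not cover tests or consultations. With one value per patient, time has a single level, and a patient random effect cannot be separated from residual error. The ANCOVA has no covariate, and the baseline test that would trigger it has no data.

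**The case against.** The strongest reply is that the outcome was never meant as a total cost. Its definition names usual-care items at the BHU, and the Discussion can be read as asking how exercise changes those costs. Read that way, the measure is not biased. This stands as far as the definition goes. It does not rescue the wider statements about healthcare costs and policy, because a payer cannot judge a reduction in treatment cost while the added treatment is left uncosted. The document also does not say who pays for the sessions, so adding a delivery cost means choosing a perspective and stating it.

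Second, the costing method is referred to cited sources not available here. They might treat intervention costs, but the article names its components twice and gives its overhead rule, and nothing in it indicates that programme costs are added.

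Third, a reader might infer more than the document supports:

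- **That the sign of the cost comparison would reverse.** Staff-hours cannot show this without a wage, a usual-care cost and a saving.
- **That the AEMC versus CAE contrast is biased to the same degree.** The Background puts the cost hypothesis on that contrast. Both arms have the same session frequency, length, site and stated staffing, so supervision largely cancels if class sizes are similar. Differences in equipment or room cost may remain but are not quantified.
- **That the analysis will use the wrong scale.** The log rule applies only if costs are non-normal. If it is triggered, it compares geometric means, whereas a budget depends on arithmetic means.

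On the missing pre value, one could split the 6 months into shorter periods to create a time factor. The plan does not say so, and it would still give no pre-intervention value.

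**Conclusion.** The point holds in two parts.

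Read as the total cost of treating a patient, the outcome understates both exercise arms against control by the full delivery cost. The direction is certain under that reading. The supervision component is 3.8 to 7.7 staff-hours per patient, assuming 1 h sessions, all four staff present throughout and all planned patients counted; smaller classes would make it larger. Its monetary size cannot be derived from the document.

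Independently of how the outcome is read, the cost analysis cannot be run as written, because it requires a pre-intervention cost that is not collected.

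This concerns a secondary outcome and leaves the primary depression outcome untouched. It should still be corrected, because the document gives the cost result an explicit policy role.

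**What to change.** **Cost measure.** Choose one:

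- Add a per-patient delivery cost (staff, room, equipment) to the CAE and AEMC arms, state the payer perspective, and report costs with and without it.
- Label the outcome as BHU care cost excluding the intervention, and limit the policy conclusions to that.

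**Analysis.** Either extract the 6 months before randomisation from the same records and use that cost as a baseline covariate, or compare the 6-month costs between groups without a time factor. Report the between-group difference in arithmetic mean cost with a confidence interval, for example by bootstrap, even if a log-scale analysis is also run.

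**Price.** Some costing work is needed and, if the baseline is added, extraction and pricing of six further months of records for 75 patients. Relabelling the outcome and dropping the time factor would cost almost nothing. Once delivery is counted, the exercise arms will look less cheap.
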